#### **4.4 Follow-up phase**

All patients will have a follow-up visit scheduled 4 weeks (28 days) after the last dose of study treatment to capture AEs and SAEs that may have occurred after discontinuation from the study treatment. Beyond these 28 days, any serious adverse events that are suspected to be related to the study drug and occur within the next 8 weeks (56 days) will also be collected. Medications/therapies given to the patient in treatment of SAEs during the 8 weeks after study treatment discontinuation must be recorded on the Concomitant Medications/Significant Non-Drug Therapies CRF, unless the patient begins a non-study anti-angiomyolipoma therapy, at which time collection of SAEs, AEs and concomitant medications will cease. Patients without angiomyolipoma progression at the time of discontinuation of study treatment will be followed with CT/MRI tumor assessments annually until eventual angiomyolipoma progression, the start of any non-study systemic anti-angiomyolipoma therapy, withdrawal of consent, or until end of the study, whichever occurs first. During this follow up period, the site will continue to send CT/MRIs for central review, and use of non-study systemic anti-angiomyolipoma therapies will be recorded.

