### Follow-up for toxicities

Patients whose treatment is interrupted or permanently discontinued due to an adverse event or abnormal laboratory value suspected to be related to study treatment must be followed at least weekly until the adverse event or abnormal laboratory value resolves or returns to grade 1. If a patient requires a dose delay of  $\geq 6$  weeks from the intended day of the next scheduled dose, then the patient must be discontinued from the study.

All patients will be followed for adverse events and serious adverse events for 4 weeks (28 days) following the last dose of study drug. Beyond these 28 days, any serious adverse events that are suspected to be related to the study drug and occur within the next 8 weeks (56 days) will also be collected. Any medication/therapy given during these 12 weeks will be recorded on the CRF.

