- All patients will have a follow-up visit 4 weeks (28 days) after the last dose of the study treatment. During this visit, AE and SAE information will be collected and recorded on the appropriate CRFs. Patients will also be followed for an additional 8 weeks (56 days) for collection and recording of any SAEs that are suspected to be related to study drug. In addition, any medication/therapy taken during these 8 weeks (56 days) will be recorded on the **Concomitant medications/Significant non-drug therapies CRF page**. If the patient is unable to return to the clinic, the investigator or his/her designee will contact the patient or caregiver via telephone to collect this information.
- All patients who are discontinued from study treatment for any reason other than angiomyolipoma progression will continue to have kidney CT/MRIs performed annually until eventual angiomyolipoma progression, the start of any non-study systemic anti-angiomyolipoma therapy, withdrawal of consent, or until end of the study, whichever occurs first. Radiological studies will be sent for central review during this follow-up period. The investigator or his/her designee will collect information on the initiation of additional anti-angiomyolipoma therapies every month. This information may be obtained during a telephone call and will be recorded in the source documents as well as on the Non-Study Systemic Anti-angiomyolipoma Therapy CRF page.

All patients must have evaluations for 4 weeks (28 days) after the last dose of study treatment (and an additional 8 weeks (56 days) for collection and recording of any SAEs that are suspected to be related to study drug). Patients lost to follow up should be recorded as such on the End of Treatment CRF. Patients who require angiomyolipoma-related surgery should discontinue the study drug before the surgery. Patients who discontinue study drug before completing the study should be scheduled for a visit as soon as possible, at which time all of the assessments listed for End of Treatment visit will be performed. At a minimum, all

patients who discontinue study treatment, including those who refuse to return for a final visit, will be contacted for safety evaluations at 12 weeks (84 days) after the last dose of study drug.

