### 7.8.1

## 8 Safety monitoring

### 8.1 Serious adverse event reporting

To ensure patient safety, every SAE, **regardless of suspected causality**, occurring after the patient has provided informed consent and until 4 weeks after the patient has stopped study treatment/participation must be reported to Novartis within 24 hours of learning of its occurrence. Any SAEs experienced after this 4-week period (**for up to 12 weeks (84 days)**) should only be reported to Novartis if the investigator suspects a causal relationship to the study drug. Recurrent episodes, complications, or progression of the initial SAE must be reported as follow-up to the original episode within 24 hours of the investigator receiving the follow-up information. An SAE occurring at a different time interval or otherwise considered completely unrelated to a previously reported one should be reported separately as a new event.

Information about all SAEs is collected and recorded on the Serious Adverse Event Report Form. The investigator must assess and record the relationship of each SAE to each specific

study drug (if there is more than one study drug), complete the SAE Report Form in English, and send the completed and signed form by fax within 24 hours to the local Novartis Integrated Medical Safety.

The telephone and fax number of the contact persons in the local department of Pharmacovigilance Operations, specific to the site, are listed in the investigator folder provided to each site. The original copy of the SAE Report Form and the fax confirmation sheet must be kept with the CRF documentation at the study site.

Follow-up information is sent to the same person to whom the original SAE Report Form was sent, using a new SAE Report Form stating that this is a follow-up to the previously reported SAE and giving the date of the original report. Each recurrence, complication, or progression of the original event should be reported as a follow-up to that event regardless of when it occurs. The follow-up information should describe whether the event has resolved or continues, if and how it was treated, whether the blind was broken or not, and whether the patient continued or withdrew from study participation.

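### Section 4.4 ends AE and SAE collection when another anti-angiomyolipoma therapy starts, contradicting the 28-day and 84-day windows set elsewhere in the protocol

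*Protocol*

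**What the plan says.** Section 4.4 (Follow-up phase) begins without conditions: "All patients will have a follow-up visit scheduled 4 weeks (28 days) after the last dose of study treatment to capture AEs and SAEs". It then adds 56 days for SAEs suspected to be related to study drug. The sentence after that concerns which therapies go on the concomitant-medication form, and it carries the exception: "unless the patient begins a non-study anti-angiomyolipoma therapy, at which time collection of SAEs, AEs and concomitant medications will cease".

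The other sections that set post-treatment safety windows contain no such exception:

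- Section 6.1.2, under Follow-up for toxicities: "All patients will be followed for adverse events and serious adverse events for 4 weeks (28 days) following the last dose of study drug". Suspected-related SAEs are collected for a further 56 days.
- Section 6.7.4: "All patients must have evaluations for 4 weeks (28 days) after the last dose of study treatment". Everyone who discontinues, including a patient who declines the final visit, is also to be contacted about safety at 84 days.
- Section 7.6.1: AE monitoring lasts at least 28 days after the last dose.
- Section 8.1: every SAE, whatever its cause, "occurring after the patient has provided informed consent and until 4 weeks after the patient has stopped study treatment/participation must be reported to Novartis". Later SAEs, up to 84 days, "should only be reported to Novartis if the investigator suspects a causal relationship to the study drug".
- Table 7-1 footnote n and Table 7-2 footnote j: the same 28-day and 84-day windows. The synopsis repeats them.

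**The concern.** A site whose patient moves to another anti-angiomyolipoma therapy soon after the last dose has two incompatible instructions. Section 4.4 tells it to stop collecting AEs and SAEs. Section 8.1 tells it to report every SAE for four weeks within 24 hours of learning of it, and suspected-related SAEs for longer.

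At stake is complete safety ascertainment in the weeks just after exposure. With 66 patients planned on RAD001, individual serious events matter. If some sites follow 4.4 and others follow 8.1, the length of safety follow-up also depends on which section a site read.

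**Working it through.** **Step 1. Reproduce the stated window.** Section 4.4 gives 28 days, then 56 more for suspected-related SAEs: 28 + 56 = 84 days, or 4 + 8 = 12 weeks. This matches the 84-day total in Section 8.1 and in the footnotes to Tables 7-1 and 7-2. The windows agree with one another; only the exception does not fit.

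**Step 2. Set the rules side by side.**

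| Place | All-cause AE/SAE | Suspected-related SAE | Ends early at new therapy? |
|---|---|---|---|
| 4.4 | 28 days | to day 84 | Yes |
| 6.1.2 | 28 days | to day 84 | No |
| 6.7.4 | 28 days | to day 84, plus contact at day 84 | No |
| 7.6.1 | at least 28 days (AEs) | not stated | No |
| 8.1 | 4 weeks (SAEs) | to day 84 | No |
| Tables 7-1 (n) and 7-2 (j) | 28 days | to day 84 | No |

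**Step 3. Does the exception reach the first 28 days?** It must, as written. It names AEs as well as SAEs, and AEs in general are scheduled for collection only up to day 28. Ending AE collection therefore has an effect only inside that window.

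**Step 4. How early can it apply?** Section 6.7.4 lists a new treatment for the indication among the reasons for discontinuation, so a new therapy can start at or close to day 0.

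**Step 5. Loss for a patient starting new therapy on day d, if 4.4 is followed.** All-cause AE/SAE days lost = max(0, 28 − d). Suspected-related SAE days lost = max(0, 84 − d).

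| d | All-cause days lost | Suspected-related SAE days lost |
|---|---|---|
| 0 | 28 − 0 = 28 | 84 − 0 = 84 |
| 14 | 28 − 14 = 14 | 84 − 14 = 70 |
| 28 | 28 − 28 = 0 | 84 − 28 = 56 |
| 56 | 0 | 84 − 56 = 28 |

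The columns overlap, because the 84 days include the first 28. At d = 0, for example, 84 calendar days are affected, not 112: all AEs and SAEs for the first 28, and suspected-related SAEs only for the other 56.

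**Step 6. How many patients?** The protocol gives no rate of starting another therapy within 84 days of the last dose, so no count can be derived.

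**The case against.** The strongest defence is that the clause does little harm. It sits in a sentence about concomitant-therapy entries and speaks of collection, whereas Section 8.1 separately sets the duty to report SAEs to the sponsor and nothing in 4.4 claims to amend it. Section 6.7.4 adds a safety contact at 84 days for all who discontinue. A site following those two sections would still capture the serious events. This stands in part: loss of SAEs is possible but not certain, and non-serious AEs in the first 28 days are the more exposed.

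A second defence is that the clause is a deliberate exit rule. Section 6.7.5 lists a new treatment among the reasons for completing study evaluation, and 4.4 and 6.7.4 end annual imaging at the start of non-study systemic therapy. This fails for safety data. Section 8.1 makes reporting mandatory until four weeks after treatment or participation stops, and the 28-day evaluations and 84-day contact in 6.7.4 cover every patient who discontinues.

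Two stronger readings are tempting, and the document does not support them:

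- A reader might take the 7% versus 0% discontinuing for adverse reactions in Section 1.4.5 and infer that 66 × 0.07 = 4.6, about 5, RAD001 patients are affected. That rate is for stopping because of toxicity in a renal cell carcinoma trial. It is not the rate of starting another angiomyolipoma therapy, and the synopsis says no treatment is approved for angiomyolipoma.
- A reader might infer that drug-related SAEs will be under-reported unequally by arm. No figure shows this. Placebo patients who progress may be offered open-label RAD001, which is study treatment and does not trigger the clause.

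**Conclusion.** The contradiction is real and lies in the current text. One clause in Section 4.4 conflicts with Sections 6.1.2, 6.7.4, 7.6.1 and 8.1 and with the footnotes to both visit schedules. Its size per affected patient is at most 28 − d days of all-cause AE/SAE collection and at most 84 − d days of suspected-related SAE collection, overlapping. These are upper bounds: they assume that the site follows 4.4 in preference to the other sections. The number of patients affected is unknown and may be small. The finding is one of incompatible instructions and avoidable risk to safety ascertainment; bias between arms is not demonstrated. It should be corrected.

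**What to change.** Remove the wording in Section 4.4 that ends AE and SAE collection at the start of a non-study anti-angiomyolipoma therapy, so that the windows in 6.1.2, 6.7.4, 7.6.1 and 8.1 apply to every patient. No new data item is needed for non-study systemic therapy: 4.4 already requires its use to be recorded, and 6.7.4 collects the start of additional therapies monthly on a dedicated form. Use that start date to present post-treatment events before and after the new therapy.

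The cost is one clause in an amendment and probably a few extra AE/SAE records. While the sentence is open, its concomitant-therapy period needs separate reconciliation: 8 weeks in 4.4 and 6.7.3, 12 weeks in 6.1.2, and 28 days in Table 7-1 footnote m. Removing the AE/SAE wording does not settle that difference.

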#### **4.5 Extension phase**

There are two distinct parts of this trial, the core and extension phase. The core phase is from the start of the trial up to the time when the results of the final primary analysis are known. This primary analysis will be performed using all data up to the data cutoff date, which is defined as 6 months after the last patient is randomized. Following a database freeze, the statistical analysis will be performed. During this time, patients will continue on the blinded treatment phase or open-label phase as before, until the time when the results of the final data analysis are known and the core phase of the trial is terminated.

If this final data analysis fails to show superiority of RAD001 over placebo, all patients will be discontinued from the study and will have end of treatment evaluations as indicated in [Table 7-1](#) and [Table 7-2](#). In this case there will be no extension phase.

If the final trial results favor RAD001, then an extension phase will be launched. All patients still receiving study treatment at this time, as well as those being followed for post-treatment evaluation, will be given the option of starting open-label RAD001. Similarly, patients receiving open-label RAD001 at the end of the core phase will be offered to continue into the extension period. The extension phase will run until 4 years after the last patient was randomized, ensuring patient follow-up of 4-5 years (assuming patient accrual over a period of approximately 12 months).

Those patients entering the extension phase, who had previously only been receiving placebo, will have scheduled assessments beginning at Treatment Day 1 according to [Table 7-2](#). Patients that had been on active RAD001 prior to beginning the extension phase will simply continue their sequence of assessments, according to [Table 7-1](#) and [Table 7-2](#). Accordingly, patients that had been on active RAD001 in the Open-label phase prior to beginning the extension phase will simply continue their sequence of assessments according to [Table 7-2](#). Patients in the extension phase will continue to have the same safety and efficacy assessments as in the core phase until angiomyolipoma progression, with the exception of biomarker assessments and pharmacokinetic assessments which will not be performed in the extension phase.

RAD001 will be provided free of charge by Novartis during the extension phase and until such time when the patient has to stop treatment with RAD001 because of adverse event(s), abnormal laboratory value(s), angiomyolipoma progression, the patient's condition no longer requires RAD001 therapy, withdrawal of consent, lost to follow-up, death, Novartis discontinues development of RAD001 for this indication, or end of the extension phase, whichever comes first. For all patients receiving RAD001 at the end of the extension phase, RAD001 will continue to be provided free of charge for as long as the medication is not commercialized and added to the list of reimbursed medications for patients with TSC.

**Figure 4-1 Study flowchart**

[figure not shown]

**Safety Follow Up:** Collection of AEs and SAEs that occur within 28 days following treatment discontinuation. SAEs suspected to be related to study drug will be collected for an additional 8 weeks (56 days).

**Post Treatment Evaluations:** CT or MRI of the kidneys (and MRIs of the brain, if applicable) annually.

**Open Label Evaluations:** CT or MRI of the kidneys (and MRIs of the brain, if applicable) to be done 12, 24 and 48 weeks after the start of open label RAD001 and annually thereafter. Safety and efficacy assessments to be carried out as in the blinded treatment phase (with the exception of biomarker and pharmacokinetic assessments, which will not be done in the open label phase).

## 4.6 Non-interventional follow-up phase

For patients who permanently discontinue everolimus (off-study) at the completion of the extension phase for reasons other than angiomyolipoma progression, a single CT/MRI scan of the kidney will be collected one-year after the last study treatment date. If angiomyolipoma bleeding ( $\leq$  grade 2) occurs, or if intervention is needed at any time during this one-year non-interventional period, a CT/MRI will be completed prior to starting any intervention and the patient will discontinue this non-interventional follow-up phase. Interventions include treatment with systemic mTOR inhibitors such as everolimus or rapamycin, embolization, or (partial) nephrectomy. These additional CT/MRIs will be sent for central review. Any use of non-study systemic anti-angiomyolipoma therapies will be recorded during this supplementary one-year period.

Patients who do not have angiomyolipoma progression at the time treatment discontinuation from the extension phase and are being followed with CT/MRI tumor assessments will exit the study, unless the patient qualifies and elects to participate in the non-interventional follow-up phase. Patients who previously discontinued treatment with everolimus during the extension phase and have not yet taken their first annual CT/MRI may also be included in this non-interventional follow-up phase, if otherwise eligible.

Patients must report to the site any angiomyolipoma-related bleeding events. Diagnostic procedure(s) pertaining to angiomyolipoma-related bleeding should also be reported. All other adverse events that may occur within the one-year period will be collected, as reported by the patient for the DS&E database.

Concomitant medications and non-drug therapies given in treatment of angiomyolipoma or angiomyolipoma-related disease progression must be reported. All other concomitant medications and non-drug therapies will only be collected, as reported by the patient for the DS&E database.

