### 4.3 Open label treatment phase

If angiomyolipoma progression (as defined in [Section 7.5.2](#)) is documented by central radiology review or an angiomyolipoma-related bleeding of grade 2 or worse (NCI CTCAE, version 3.0) during the blinded treatment phase, then the treating physician may proceed to unblind the patient. Central radiology review of the CT/MRIs will be completed no later than 3 weeks after receipt by the central reviewer, so the unblinding may not be able to take place until up to 3 weeks after the progression was actually observed. However, if progression was unequivocal according to the local radiologist, then the investigator should contact the Novartis Clinical Trial Head (CTH) or designee to proceed with unblinding without waiting for confirmation from central radiology review.

Following unblinding, patients who had been receiving placebo may be offered open-label treatment with RAD001 if the treating physician believes the patient could benefit from this therapy.

For the open-label phase of the study, the most recent kidney CT/MRI from the blinded treatment phase of the study will be used as the baseline, and further kidney CT/MRIs will be conducted at 12, 24 and 48 weeks after the start of open-label RAD001, and annually thereafter, until angiomyolipoma progression, unacceptable toxicity or discontinuation for any other reason. An additional CT/MRI of the kidney will be obtained at End of Treatment in the open-label RAD001 phase, provided discontinuation was not for angiomyolipoma progression and if it had been more than 8 weeks since the most recent CT/MRI of the kidney during the

first year of open-label treatment or more than 6 months since the most recent CT/MRI thereafter. For each patient, the same imaging modality should be used throughout the trial. All kidney imaging scans obtained in the open-label phase of the trial will be sent in for central radiological review within 2 days of the scan.

Patients receiving open-label treatment with RAD001 will continue having safety and efficacy assessments as in the blinded treatment phase, as described in the Visit Evaluation Schedule provided in [Table 7-2](#), with the exception of biomarker and pharmacokinetic assessments which will not be performed in the open-label phase.

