Open-label treatment with RAD001 will continue until the patient again presents with angiomyolipoma progression (second occurrence) which is either radiologically documented or is an angiomyolipoma-related bleeding of grade 2 or worse (NCI CTCAE, version 3.0). At this point, the patient will be discontinued from the study and will enter the follow-up phase.

The investigator or his/her designee will **not** disclose patient unblinding information to the central radiology reviewers. Due to the unblinding of a subset of patients upon angiomyolipoma progression, members of the Novartis clinical trial team may become unblinded to an individual patient's treatment during the conduct of the trial including team members involved in source data verification. The blinding of the central radiology review, the basis for the primary analysis of the primary endpoint of the trial, will be maintained despite the planned unblinding.

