| 
a. For all patients participating in this non-interventional follow-up phase, kidney CT/MRI should be performed at the beginning of this period, if not done within the past 2 months. For each patient same imaging modality must be used.
 
b. The kidney CT/MRI scan at the end of the non-interventional follow-up phase should be obtained prior to the initiation of an intervention or within 3 weeks of the 1-year anniversary of the last dose of study treatment, whichever comes first. Interventions include commercial everolimus, off label rapamycin, embolization or nephrectomy at any time during this 1-year period.
 
c. The EOT for the extension phase is 779.
 
d. CRF for Study Evaluation Completion will only be completed at the end of all study-related activity, including any long-term follow-up assessments when the patient is not taking study drug
 
e. Angiomyolipoma-related bleeding, diagnosis, and concomitant medications and non-drug therapies given in treatment of angiomyolipoma or angiomyolipoma-related disease progression should be captured on the CRF. Other adverse events and other concomitant medications will only be captured as reported by the patient for the DS&E database.
 |                        |                                               |                                    |                                                                          |

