### 10.4.1 Variable

The primary endpoint of this study, angiomyolipoma response rate, is defined as the proportion of patients with an angiomyolipoma response, as defined in [Section 7.5.2](#), using data from the Independent Central Radiological Review of CT/MRIs and the Adverse Events CRF page (to identify angiomyolipoma-related bleeding of grade 2 or worse as defined by NCI CTCAE version 3.0).

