### 10.5.11 Evaluation after everolimus discontinuation

Patient who discontinue everolimus for reasons other than angiomyolipoma progression, and who subsequently do not receive systemic treatment with an mTOR inhibitor, will be analysed specifically. Data included in this analysis will be data from the follow-up phase (until the end of the extension phase) and/or from the non-interventional follow-up phase.

Reasons for everolimus discontinuation and for non-inclusion in the non-interventional follow-up phase will be presented for this population. A table of demographic characteristics at start of everolimus and duration of everolimus treatment will be produced in order to appreciate the selection biases.

Sum of volumes of target angiomyolipoma lesions (the ones identified before the start of everolimus) will be described at the time of everolimus discontinuation (end of treatment visit or non-interventional follow-up entry visit) and at the time of the one-year follow-up scan (i.e. scan performed one year after everolimus discontinuation), or an earlier scan which was performed following an angiomyolipoma-related bleeding event ( $\geq$  grade 2), or prior to any intervention such as the start of systemic mTOR treatment, embolization or nephrectomy.

The effect of stopping everolimus on tumor growth will be described in terms of change and percentage change in the sum of the angiomyolipoma target lesions volume from the start of everolimus and from the time of everolimus discontinuation (scan performed at the end of everolimus treatment). Individual plots of sum of volumes of target angiomyolipoma lesions by time will also be performed to illustrate the tumor evolution after stopping everolimus. Similar analyses will be conducted to describe the changes in kidney volume.

The number of patients with at least one new angiomyolipoma lesion  $\geq 1.0$  cm in longest diameter and one angiomyolipoma-related bleeding of grade  $\geq 2$  assessed at the one-year follow-up scan will be tabulated.

If the number of patients included in this analysis is sufficient, the angiomyolipoma progression rate one year after everolimus discontinuation will be provided with exact 95% confidence intervals (Clopper and Pearson 1934). The angiomyolipoma progression will be defined as in Section 7.5.2 of the protocol, i.e. one or more of the following criteria should be observed at the one-year follow-up scan:

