- an increase from nadir of 25% or more in angiomyolipoma volume to a value greater than value just prior to everolimus starting date (where angiomyolipoma volume is the sum of the volumes of all target angiomyolipomata identified prior to everolimus start and where nadir is the lowest angiomyolipoma volume achieved by the patient previously in the everolimus period (including the value just prior to everolimus starting date))
- an increase from nadir of 20% or more in the volume of either kidney to a value greater than value just prior to everolimus starting date, where nadir is the lowest kidney volume obtained for the patient, separately for each kidney, previously in the everolimus period (including the value just prior to everolimus starting date)
- the appearance of a new angiomyolipoma  $\geq 1.0$  cm in longest diameter
- angiomyolipoma-related bleeding grade  $\geq 2$  as defined by NCI CTCAE, version 3.0.

In addition, if most patients have small AML lesions (less than 1 cm) at the end of everolimus treatment, the sum of the angiomyolipoma target lesions volume identified at the end of

everolimus treatment with a diameter greater than 1 cm will be described at the time of everolimus discontinuation and at the one-year follow-up scan. The change and percentage change in volume from the time of everolimus discontinuation will also be presented.

If the number of patients included in this analysis is sufficient, the angiomyolipoma progression rate 1-year following everolimus discontinuation will be provided with exact 95% confidence intervals (Clopper and Pearson 1934). The angiomyolipoma progression following everolimus discontinuation will be defined as one or more of the following:

- an increase of 25% or more in angiomyolipoma volume from the end of everolimus treatment (where angiomyolipoma volume is the sum of the volumes of target angiomyolipomata identified as greater than 1 cm at the time of everolimus discontinuation)
- an increase of 20% or more in the volume of either kidney from the end of everolimus treatment
- the appearance of a new angiomyolipoma  $\geq 1.0$  cm in longest diameter
- angiomyolipoma-related bleeding grade  $\geq 2$  as defined by NCI CTCAE, version 3.0.

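### Section 4.6 reverses the bleeding threshold for early exit from off-drug follow-up (≤ grade 2 where the rest of the protocol has ≥ grade 2)

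*Protocol*

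**What the plan says.** Section 4.6 covers patients who stop everolimus for good at the end of the extension phase for reasons other than progression. For them, "a single CT/MRI scan of the kidney will be collected one-year after the last study treatment date". The exception is an early exit: "If angiomyolipoma bleeding ( $\leq$ grade 2) occurs", or if an intervention is needed during the year, a CT/MRI is done before any intervention and the patient leaves the phase.

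Section 10.5.11 analyses these scans. It uses the one-year scan or an earlier one done "following an angiomyolipoma-related bleeding event ( $\geq$ grade 2), or prior to any intervention" (systemic mTOR treatment, embolization or nephrectomy). Its off-drug progression definitions include "angiomyolipoma-related bleeding grade $\geq 2$ as defined by NCI CTCAE, version 3.0", and Section 7.5.2 has the same criterion.

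Elsewhere the threshold is written in words. Section 4.3 allows unblinding after "angiomyolipoma-related bleeding of grade 2 or worse (NCI CTCAE, version 3.0) during the blinded treatment phase" and ends open-label treatment at a second progression that is radiologically documented "or is an angiomyolipoma-related bleeding of grade 2 or worse (NCI CTCAE, version 3.0". Section 10.4.1 uses the Adverse Events CRF "to identify angiomyolipoma-related bleeding of grade 2 or worse as defined by NCI CTCAE version 3.0".

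Footnote b of Table 7-3, the visit schedule for this phase, wants the exit scan "obtained prior to the initiation of an intervention or within 3 weeks of the 1-year anniversary" of the last dose, whichever comes first. It does not mention bleeding.

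**The concern.** Section 4.6 is an operative instruction to sites: it decides who leaves the phase and when the scan is taken. As printed, it removes patients with mild bleeding and keeps those with severe bleeding. No rationale is given, and the rule conflicts with the section that uses the resulting scans.

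The phase exists to show what happens to angiomyolipoma volume in the year after stopping everolimus, and it rests essentially on one scan per patient. If a site follows Section 4.6 to the letter, a one-year scan lost after a grade 1 bleed cannot be recovered.

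**Working it through.** The plan gives no figure to reproduce on this point. The check compares the rules as written.

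**Count of threshold statements.** Statements that set bleeding at grade ≥ 2 or grade 2 or worse:

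- Synopsis, endpoints (response and progression): 2
- Section 4.3: 2, both in words
- Section 7.5.2 (response and progression): 2
- Section 10.4.1: 1, in words
- Section 10.5.11 (early scan, tabulation of bleeds, two progression definitions): 4

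Total: 2 + 2 + 2 + 1 + 4 = 11, of which 3 are in words. Statements in the opposite direction: 1, in Section 4.6.

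**Rule by grade.** Section 7.6.1 uses CTCAE grades 1 to 4. Literal Section 4.6 requires the early scan if grade ≤ 2 or an intervention is needed. Section 10.5.11 lists an early scan if grade ≥ 2 or an intervention follows.

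| Bleed, no intervention | Section 4.6 as written | Section 10.5.11 | Agree? |
|---|---|---|---|
| Grade 1 | scan and exit | not listed | no |
| Grade 2 | scan and exit | listed | yes |
| Grade 3 | no trigger | listed | no |
| Grade 4 | no trigger | listed | no |

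Agreement is 1 of 4 grades without an intervention. With an intervention, both rules give an early scan at every grade, 4 of 4. This compares rules; it says nothing about how often they would differ in practice.

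**Consequence by grade, no intervention.**

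- *Grade 1.* The patient exits and the one-year scan is lost. The early scan is not one that Section 10.5.11 lists for its volume summary, though it could still appear in the individual plots. The first off-drug progression rate in that section requires its criteria to be observed at the one-year scan, so that assessment is lost too. For illustration, a grade 1 bleed at month 3 would forfeit 12 − 3 = 9 of the 12 off-drug months.
- *Grade 3 or 4.* Nothing is triggered under Section 4.6, although the event is progression under Sections 7.5.2 and 10.5.11. The patient stays in follow-up and the one-year scan is still due. The bleed is recorded on the CRF (Table 7-3, footnote e). Only the early volume measurement is missing.

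**The case against.** The strongest reply is that this is a typographical slip in one symbol whose intended meaning is obvious, and that a conversion error in the file cannot be fully excluded. Part of that stands: nothing suggests that ≤ was deliberate, and the sponsor should check its master copy. But the ≥ sign appears correctly in the other symbolic bleeding thresholds, and the three statements in words fix the intended direction without relying on any symbol.

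A second reply is that other instructions would rescue the scan. Table 7-3 footnote b and Section 7.5.1 ask for the exit scan only before an intervention or at one year. The synopsis ties early exit to progression, which for bleeding means grade ≥ 2, or to an intervention. Section 4.6 itself gives no scan timing for a bleed without an intervention. A site working from the schedule might therefore still obtain the one-year scan. This is fair, and it makes the loss conditional on following Section 4.6. It does not remove the contradiction: Section 4.6 says in terms that the patient leaves the phase, and Section 7.5.1 sends the reader to Section 4.6 as well as to Table 7-3.

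Third, the stakes are small. The analysis is descriptive, its progression rate is reported only if enough patients are available, and severe bleeds that lead to an intervention still trigger the scan. All of this is accepted and limits the size of the point.

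**Conclusion.** The concern holds. Section 4.6 states the bleeding trigger in the wrong direction, against eleven statements elsewhere, including the one in Section 10.5.11 that governs the same early scan. Taken literally, it agrees with Section 10.5.11 at one of four grades when there is no intervention. It loses the one-year scan after a grade 1 bleed and the early scan after a grade 3 or 4 bleed.

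The effect is limited to the descriptive evaluation after everolimus discontinuation. The primary endpoint, time to angiomyolipoma progression, skin lesion response and type I error are not affected. The protocol gives no expected number of bleeds in this phase, so the number of patients affected is unknown. The conclusion assumes that the printed symbol is the sponsor's text and that sites act on Section 4.6. It should be corrected because the missing scans would be irrecoverable and the correction is small.

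**What to change.** After checking the symbol against the master copy, change ≤ grade 2 to ≥ grade 2 in Section 4.6. Add the same grade ≥ 2 bleeding trigger to footnote b of Table 7-3, so that the visit schedule and the text give one instruction, and notify sites. Section 7.5.1 already refers to both places and needs no separate edit.

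This brings the bleeding trigger into line with Sections 10.5.11 and 7.5.2. It does not bring it into line with the synopsis, whose exit trigger is broader (any angiomyolipoma progression).

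The cost is one symbol, one clause and a site notice. Under Section 11 the change must go through a written amendment with ethics approval and, where required, health authority approval; it can be carried in the next amendment, but sites should be told before patients in this phase are managed under the wrong rule.
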